### Sample size calculation

Given an attrition rate of 15% at follow-ups, a sample of 60 (*N* = 60) will provide 80% power to detect an effect size of 0.8 (referencing highly effective psychotherapy studies) [31] on the primary outcome measure of the Maslach Burnout Inventory–General Survey (MBI-GS) [4] between the intervention and control groups at a (two-tailed test) 5% level of significance.

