### Participants

The sample will comprise 60 EoL care professionals. Recruitment will be conducted at all five HCA service centers (i.e., one daycare and four satellite service centers) concurrently via four non-overlapping consecutive recruitment rounds. Each round will recruit 14 or 16 participants; seven or eight participants will be randomly assigned to one intervention group, and seven or eight participants will be randomly assigned to one control group, adhering to a waitlist RCT design. Participants will be recruited through the medical director of HCA and his appointed staff with the support of a study initiation presentation conducted by the research team during a regular monthly organization meeting with all clinical and program staff. This presentation serves as a study invitation, informing potential participants of MCAT’s basic background and essential research procedures, and includes the request for participants to keep their MCAT experiences private until study completion so as to reduce the potential for intervention contamination. Participants will be invited to join the research with the understanding that they will be given allocated time during regular working hours to participate in the MCAT intervention without any financial implications on their part; they are also assured that refusal to participate is respected and would not result in any negative consequences. Inclusion criteria include EoL care professionals (at least 21 years old) who are fluent in written and spoken English. Exclusion criteria include the inability to provide informed consent or major depression (or other mental health conditions) or both. Written informed consent will be obtained from all participants before study participation. Participants’ confidentiality will be safeguarded under this ethical provision.

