### Intervention group

MCAT will be delivered by an accredited art therapist with a master’s degree in art therapy, together with one clinical researcher with a doctorate in thanatology who is also a certified mindfulness practitioner. The two MCAT therapists will work together and collaboratively to render a full 6-weekly, 18-h, group-based intervention. Each MCAT group will be heterogeneous and include a mix of seven or eight participants who may be physicians, nurses, social workers, and allied health and program workers. Each of the 6-weekly MCAT sessions will cover a unique topic that aims to promote understanding, acceptance, and compassion of self and others for cultivating resilience and shared meaning. The topics will be strategically designed to build upon one another week by week with a scaffolding of themed meditations, guided visualizations, and art activities that deepen participants’ cognitive awareness and emotionality, empowering them to fully experience and appreciate the authenticity and immediacy of their self-reflection, creative expression, and group sharing. Table 1 provides a summary of the topics and experiential activities of the 6-week MCAT intervention model.

**Table 1 Tab1:** Overview of therapeutic elements of the mindful-compassion art therapy intervention model

Session	Topic	Mindfulness meditation	Visualization theme	Art therapy activities
Week 1	Self-care	Affectionate breathing	Self-kindness	Mandala of self-care / reflective art observations
Week 2	Stress management	Compassionate body-scan	Bodily stress	Symbol of stress / transformative art-making
Week 3	Positive patient care	Loving-kindness meditation	Strengths and progress in patient care	Symbol of strength / creative response writing
Week 4	Challenging patient care	Loving-kindness meditation	Weakness and stagnation in patient care	Symbol of weakness / creative response writing
Week 5	Loss and grief	Meditation on impermanence	A patient’s death	Symbol of grief / collective small group mural
Week 6	Professional purpose	Meditation on giving and receiving compassion	Wisdom learnt and meaning of work	Mandala of meaning / collective large group mural

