### Data analysis

#### Quantitative data

All quantitative data will be entered, stored, and analyzed by using SPSS statistical analysis software. Between- and within-subject comparisons of outcomes will be conducted by using repeated-measures analysis of variance (ANOVA) with the appropriate confidence interval and effect size estimates reported. Intervention and waitlist-control groups will be compared to assess intervention effectiveness on the primary outcome of burnout (continuous variable); secondary outcomes, including death attitude, emotional regulation, resilience, compassion, and quality of life (continuous variables), will also be compared to examine the potential effects of MCAT on other domains of psycho-socio-spiritual well-being. Between-subject comparisons will be conducted at T2 with baseline assessment. To explore the potential maintenance of intervention effects, within-subject comparisons will be conducted with the intervention group at T3 with baseline assessment. To examine the overall intervention effects of MCAT, within-subject comparisons will be conducted by combining the baseline-to-T2 assessment scores for the intervention group and the T2-to-T3 assessment scores for the waitlist-control group. Multi-level analysis will be conducted to characterize and predict changes in all outcomes. Intervention and waitlist-control groups will also be compared on demographic characteristics and baseline measures. If necessary, these will be controlled in the analyses. Exploratory analyses on the influence of nature or work and years of professional EoL care experience on main outcomes and secondary outcomes will also be carried out. Finally, recruitment rates as well as comparisons of dropout rates and missing data in the two groups will be reported.

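### The stated 80% power and the repeated-measures ANOVA treat participants as independent, although MCAT is delivered in four groups of 7–8; neither holds if outcomes correlate within groups

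*Protocol article*

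**What the plan says.** All references are to the protocol article.

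- **Sample size calculation:** 60 participants with 15% attrition "will provide 80% power to detect an effect size of 0.8 (referencing highly effective psychotherapy studies"; the outcome is the MBI-GS and the test is two-tailed, at the "5% level of significance". No ICC or design effect is mentioned.
- **Participants:** there are four consecutive recruitment rounds. In each, "seven or eight participants will be randomly assigned to one intervention group" and the same number to one control group.
- **Intervention group:** the same two therapists "work together and collaboratively to render a full 6-weekly, 18-h, group-based intervention". The sessions include peer responses to art, joint murals and small and large group discussion.
- **Data analysis, Quantitative data:** between- and within-subject comparisons use repeated-measures ANOVA. Arms are compared at T2 with baseline, before the waitlist arm is treated. A pooled pre-post analysis combines the treated periods of both arms. No therapy-group or round term is named. A separate sentence adds: "Multi-level analysis will be conducted to characterize and predict changes in all outcomes".

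**The concern.** People who spend 18 hours together in one therapy group share its dynamics, and the Background section names interactive processes and connectedness as part of how MCAT is expected to work. Some correlation of outcomes within a group is therefore plausible. At T2 it would arise in the treated arm only, across four groups. In the pooled pre-post analysis it would arise in eight.

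If that correlation is positive and ignored, the variance of the treated-arm mean is understated. The interval for the treatment effect is then too narrow, the test rejects a true null more often than 5%, and the stated power is not what a correct analysis would have. With only four treated groups, a correct analysis also has few degrees of freedom for the between-group variance.

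**Working it through.** **Inputs.** From Sample size calculation: N = 60, 15% attrition, d = 0.8, two-sided 5%. From Participants: four rounds with one intervention group each. The ICC is not in the document and is assumed to lie between 0 and 0.20.

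**Step 1: reproduce the plan's figure.** Completers are 60 × 0.85 = 51, or 25.5 per arm. The noncentrality under independence is 0.8 × √(25.5/2) = 2.857. The noncentral t with 49 df gives power 79.96%. The 80% is thus the independent-participants figure and leaves no slack.

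**Step 2: inflate the treated arm only.** Completers per MCAT group are 25.5/4 = 6.375.

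- Design effect in the treated arm: DE = 1 + (6.375 − 1) × ICC.
- True over naive variance of the difference: (DE + 1)/2.
- Noncentrality: 2.857/√[(DE + 1)/2].

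At ICC 0.10, DE = 1 + 5.375 × 0.10 = 1.538, the variance ratio is 1.269, the standard error ratio is 1.13, and the noncentrality is 2.536.

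**Step 3: allow for only four groups.** With v1 = DE/25.5 and v0 = 1/25.5, Satterthwaite df = (v1 + v0)² / (v1²/3 + v0²/24.5). At ICC 0.10, v1 = 0.0603 and v0 = 0.0392, which gives df = 7.8.

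| ICC | DE | True/naive SE | Power, 49 df | Satterthwaite df | Power, Satterthwaite | Type I error if groups ignored |
|---|---|---|---|---|---|---|
| 0 | 1.00 | 1.00 | 80% | 10.7 | 74% | 5% |
| 0.02 | 1.11 | 1.03 | 78% | 9.9 | 71% | 5.6% |
| 0.05 | 1.27 | 1.07 | 75% | 8.9 | 67% | 6.7% |
| 0.10 | 1.54 | 1.13 | 70% | 7.8 | 60% | 8% |
| 0.20 | 2.08 | 1.24 | 62% | 6.4 | 50% | 11.5% |

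The last column is from simulation of an unclustered two-sample test. Runs differ by a few tenths of a point (6.5% to 6.9% at ICC 0.05). Neither power column takes credit for baseline. The ICC 0 row shows that part of the loss in the Satterthwaite column, 80% to 74%, comes from having four groups and not from correlation.

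**Step 4: shared round variance.** Allocation is balanced within rounds, so a round effect common to both arms cancels from the contrast but enlarges the naive variance. With an assumed round variance of 0.05 to 0.10, simulated type I error is about 5% at ICC 0.02, about 6% at 0.05 and 7–8% at 0.10.

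**Step 5: baseline information.** With an assumed T1–T2 correlation r = 0.5 and residual ICC 0.10, the normal approximation for baseline-adjusted power is Φ{0.8/√[0.75 × 2.5375/25.5] − 1.96} = Φ(0.97) ≈ 83%, before any small-df penalty.

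**The case against.** A reader might infer that the standard errors are certainly too small and the false-positive rate certainly above 5%. The document does not support that. It gives no ICC, and several features would hold between-group variance down: the same two therapists, the same room, a highly structured programme, deliberately mixed groups and individual randomisation within rounds. At ICC 0.02 the unclustered type I error is only about 5.6%, and shared round variance can offset that. This stands, and it makes the point conditional on the ICC.

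A reader might also infer that power is overstated for the analysis that will be run. That is not established either. The T2 comparison uses baseline, and the sample size statement takes no credit for it; with adjustment, power could reach or exceed 80%. A change-score analysis gains only if the T1–T2 correlation exceeds 0.5. Whatever the gain, it does not correct the standard error or the type I error if groups are ignored.

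The multi-level sentence could be read as covering therapy group, with its detail left to an analysis plan. But it names no levels, may mean only occasions within persons, and is given a different task from the comparison of arms. It also leaves the power figure as it is.

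Finally, the aims include feasibility and potential effectiveness, and the Discussion already concedes a small sample and a large assumed effect. It does not concede that the 80% depends on independent participants.

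**Conclusion.** The point holds in conditional form. The stated power and the named ANOVA both assume independent participants, while the treatment is delivered in four groups at T2 and eight in the pooled analysis. If outcomes correlate within MCAT groups, the ANOVA standard errors are too small and the 80% does not hold.

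Over an assumed ICC of 0.05 to 0.10, power without baseline credit is about 75% to 70% from variance inflation alone and about 67% to 60% with Satterthwaite df. Type I error is about 6.7% to 8%, lower if rounds share variance. At ICC 0.02 the variance effect is small and the limited number of groups accounts for most of the loss. At 0.20 the problem is serious. These figures assume equal attrition across arms and equal total variance in the two arms.

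**What to change.** 1. Make the T2 arm comparison a partially nested mixed model: arm, T1 score and recruitment round, a random MCAT-group effect in the treated arm only, and Satterthwaite or Kenward-Roger df.
2. In the pooled pre-post analysis, use eight MCAT-group effects.
3. State whether the planned multi-level analysis is this model, and name its levels.
4. Label the 80% as holding only under independence. Restate power over an ICC range with the df method used, noting that T1 adjustment may recover some power but does not correct the standard error if groups are ignored.

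The restated power should be computed for the exact model. The Satterthwaite figures above leave round out. Fitting round as a fixed factor reduces the df further, towards the 4 − 1 = 3 available from four within-round contrasts.

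The change needs no extra participants. The trial was in month 40 of 48 and still collecting data at writing, so the model could be fixed before analysis. The cost is wider intervals, a less favourable power statement and a group variance estimated imprecisely from four groups.

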### Intervention group

MCAT will be delivered by an accredited art therapist with a master’s degree in art therapy, together with one clinical researcher with a doctorate in thanatology who is also a certified mindfulness practitioner. The two MCAT therapists will work together and collaboratively to render a full 6-weekly, 18-h, group-based intervention. Each MCAT group will be heterogeneous and include a mix of seven or eight participants who may be physicians, nurses, social workers, and allied health and program workers. Each of the 6-weekly MCAT sessions will cover a unique topic that aims to promote understanding, acceptance, and compassion of self and others for cultivating resilience and shared meaning. The topics will be strategically designed to build upon one another week by week with a scaffolding of themed meditations, guided visualizations, and art activities that deepen participants’ cognitive awareness and emotionality, empowering them to fully experience and appreciate the authenticity and immediacy of their self-reflection, creative expression, and group sharing. Table 1 provides a summary of the topics and experiential activities of the 6-week MCAT intervention model.

**Table 1 Tab1:** Overview of therapeutic elements of the mindful-compassion art therapy intervention model

Session	Topic	Mindfulness meditation	Visualization theme	Art therapy activities
Week 1	Self-care	Affectionate breathing	Self-kindness	Mandala of self-care / reflective art observations
Week 2	Stress management	Compassionate body-scan	Bodily stress	Symbol of stress / transformative art-making
Week 3	Positive patient care	Loving-kindness meditation	Strengths and progress in patient care	Symbol of strength / creative response writing
Week 4	Challenging patient care	Loving-kindness meditation	Weakness and stagnation in patient care	Symbol of weakness / creative response writing
Week 5	Loss and grief	Meditation on impermanence	A patient’s death	Symbol of grief / collective small group mural
Week 6	Professional purpose	Meditation on giving and receiving compassion	Wisdom learnt and meaning of work	Mandala of meaning / collective large group mural

In week 1, MCAT participants will be invited to explore and examine the topic of positive self-care, beginning with a brief introduction to the concepts of mindfulness practice and expressive art for healing, followed an affectionate breathing meditation, a guided visualization on the theme of self-kindness, a facilitated art-making session for creating a mandala of self-care, and ending with reflective art observation with group sharing. A mandala, defined as a sacred circle across many spiritual traditions, is chosen as for the first art activity because the contained circular space serves as a creative constraint to promote greater creativity and self-expression among participants.  Week 2 will involve an exploration of the topic of stress management, supported by a compassionate body-scan meditation, a guided visualization on the theme of bodily stress, followed by a facilitated art-making session for creating a symbol of stress, and ending with a transformative art-making session on easing stress with group sharing. Weeks 3 and 4 will progress deeper into participants’ cognitive awareness to focus on the topics of patient-care experiences and skill building. Both weeks will begin with a loving-kindness meditation, followed by a guided visualization on a positive patient-care interaction and a facilitated art-making session on the theme of strengths and progress in week 3, and a guided visualization on the theme of challenging patient-care interaction and a facilitated art-making session on the theme of weaknesses and stagnation in week 4, and both weeks will end in creative response writing activities and group sharing. In week 5, participants will be empowered to dive deeper into their emotionality by exploring the topic of loss and grief, beginning with a meditation on impermanence, a guided visualization on the theme of a patient’s death, followed by a facilitated art-making session for creating a symbol of grief, and ending with a collective small group mural activity and group sharing. In week 6, participants will be invited to consolidate all of their experiences and learnings for weeks 1 to 5 and apply them in exploring the topic of professional purpose. This will begin with a meditation on giving and receiving compassion, a guided visualization on the theme of wisdom learnt and meaning of work, followed by a facilitated art-making session for creating a mandala of meaning, and ending with a collective group mural activity and group sharing.

In terms of the specific intervention procedures of MCAT, each weekly session will last 3 h and will comprise an integrative alignment of experiential activities that aim to foster self-reflection, creative expression, authentic sharing, and perspective widening. Table 2 provides a summary of the intervention procedures of a 3-h MCAT session, which is conducted in a medium-size activity room at the research site, equipped with moveable chairs, tables, and a collection of art materials, including acrylic paints, water color, oil and soft pastels, color pencils and markers, crayons, polymer clay, and collage materials such as old magazines, cutouts, scissors, glue, and drawing blocks. These art media serve to promote active engagement among participants of varying levels of experience and skill with the arts.

**Table 2 Tab2:** Mindful-compassion art therapy weekly session plan

Mindful-compassion art therapy activity	Time allocation	Interventionist
Check-in and review (MP and AT)	10 min	AT and MP
Mindfulness meditation with guided visualization (MP)	20 min	MP
Facilitated art-making (AT)	50 min	AT
Break	15 min	-
Mindful breathing	5 min	MP
Reflective art observation, transformative art, creative Response writing, collective mural	30 min	AT
Small group discussion	20 min	AT and MP
Large group discussion	25 min	AT and MP
Mindful breathing and checkout	5 min	MP

*Abbreviations*: *AT* art therapist, *MP* mindfulness practitioner

Each MCAT session will begin with a 10-min check-in that includes a brief introduction to the topic and activities that are covered for the day. Thereafter, the mindfulness practitioner will lead a 20-min theme-based mindfulness meditation with a guided visualization activity on specific topics as described in the preceding section and this will be immediately followed by a 50-minutue individual art-making session facilitated by the art therapist. During this time, participants will be reminded that beauty in the MCAT therapeutic space is defined by the ability to connect with and freely express their inner emotions via the creation of a tangible art object and thus the focus is on relational aesthetics rather than visual aesthetics [32]. At the 70-min mark of the 3-h session, participants will be reminded of the time and asked to put the final touches on their art pieces in a way that they are comfortable with. After a 15-min break followed by a brief 5-min mindful-breathing exercise, participants will be invited to engage in a 30-min creative activity which may involve (a) reflecting on their own art while observing the arts of others to develop an appreciation of emotional expressions (i.e., reflective art observation), (b) transforming the art objects that they have created before the break into a new art piece (i.e., transformative art), (c) observing and responding to each art object created by all of their peers with one or two written emotive words – using the response words provided by their peers, participants write a short poem or prose to describe their own art piece (i.e., creative response writing), or (d) breaking into small groups of two or three participants who created similar art objects in terms of color, shape, and themes to create a group mural elaborated by a piece of creative writing composed jointly by all group members (i.e., collective mural). Afterwards, there will be a 20-min small group discussion followed by a 25-min large group discussion, where participants are provided with the opportunity to openly share, discuss, and reflect on their creative experiences as well as the stories behind their art. The 3-h session will end with a 5-min mindful-breathing activity with checkout. If a participant expresses a desire to withdraw from the study because of emotional distress at any time during the intervention, the research team will respect their decision and provide a referral to support services rendered by the research site.

### Waitlist-control group

Participants in the waitlist-control group will receive the full 6-week MCAT intervention upon completion of all treatment procedures by intervention group and after the second baseline assessment.

### Procedures

The HCA recruitment team will be asked to distribute research information pamphlets to all eligible staff at the beginning of each recruitment round. Those who are interested to join the study will inform the HCA team and provide their verbal consent in releasing their contact information to the clinical research team. Once they recruit a sufficient number of participants for each recruitment cycle, the HCA team will forward a consolidated information sheet containing only participants’ names and telephone numbers to the clinical research team. An appointed member of the clinical research team will contact the participants and arrange a time to obtain written informed consent and conduct a face-to-face self-administrated baseline assessment (T1) followed by randomization and confirmation of the intervention schedule. Those assigned to the intervention group will attend 6-weekly MCAT sessions within 1 week after randomization; thereafter, immediate post-intervention assessment will be carried out (T2) and there will be a follow-up assessment at 6 weeks (T3). Those assigned to the waitlist-control group will complete a pre-intervention assessment at 6 weeks or after the intervention group completes all treatment procedures (T2) and thereafter attend the 6-weekly MCAT sessions followed by an immediate post-intervention assessment (T3). All MCAT interventions are conducted in the same activity room at the headquarters of HCA. Study participants' personal information will be kept confidential and only the corresponding researchers will have access to such information.

